### Sample size

There are no clear definitions or guidelines for estimating the sample size for a feasibility study [98]. According to [99], a sample size of 10–15 in a group will probably be sufficient. The proposed sample size was calculated to be 38, allowing for an estimation of the feasibility proportions of adherence and retention to within at least ±17% [100, 101] using a 95% confidence interval with a power of 80% to detect an effect size of 0.6 [77]. The main purposes of this exploratory feasibility study are to collect data to allow the design and sample size calculation for the CRCT.

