### Data analysis

All of the collected data will be cleaned prior to the analysis process. The data analysis will be conducted by a statistician who is blind to the participants’ group allocation. The participants’ demographic characteristics will be presented using descriptive statistics (mean and standard deviation) for the continuous data, including age, body height and weight plus BMI, and percentage frequencies for the categorical data, including gender, marital status and educational level. Inter-relationships between the variables will be assessed using Pearson’s correlation coefficient. Differences between the intervention and control groups on outcome indicators will be compared using *t* tests and chi-square tests for the continuous and categorical data respectively. The effect of time (baseline; 3 and 6 months after the completion of the programme) on the outcome measurements will be investigated using repeated measures analysis of variance (ANOVA). The impact of “baseline stage matching” on “stage of change” and other outcome measures within the intervention group will be compared using the Kruskal-Wallis *H* test and one-way ANOVA. Normality tests will be conducted. If the data are normally distributed, it will be appropriate to use parametric tests such as one-way ANOVA. But if they are not normally distributed, non-parametric tests such as the Kruskal-Wallis *H* test will be used. *P* values of less than 0.01 will be considered as statistically significant for all comparisons. All statistical analyses will be conducted using SPSS version 22.0. Intention-to-treat analyses will be applied. As of now, there is no clear cut-off for the acceptable proportion of missing data in a dataset for statistical data analysis. Questionnaires with missing rates of more than 10% will be regarded as “disqualified” and excluded from the analysis. Various statistical methods will be used to treat missing data, including replacement by means or values from the regression analyses, depending on the amount and type of missing data.

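### The three-visit repeated measures ANOVA needs a value at every visit, and both of the plan's stated missing-data rules serve a missed visit badly

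*Protocol article*

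**What the plan says.** All the relevant rules stand in the Data analysis section of the protocol article.

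- **Time analysis.** The factor is given as "The effect of time (baseline; 3 and 6 months after the completion of the programme", and its effect "on the outcome measurements will be investigated using repeated measures analysis of variance (ANOVA". No other analysis listed there uses the three visits jointly.
- **Analysis set.** "Intention-to-treat analyses will be applied".
- **Exclusion.** "Questionnaires with missing rates of more than 10% will be regarded as “disqualified” and excluded from the analysis".
- **Replacement.** "Various statistical methods will be used to treat missing data, including replacement by means or values from the regression analyses", with the choice left to turn on how much is missing and of what kind.
- **Group comparison.** This is a separate step: "Differences between the intervention and control groups on outcome indicators will be compared using" t tests and chi-square tests.
- **Significance level.** P "values of less than 0.01 will be considered as statistically significant for all comparisons". The software is SPSS 22.0.

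The Sample size section gives 38 as the sample size, "allowing for an estimation of the feasibility proportions of adherence and retention". Retention is therefore something the study sets out to measure, and no drop-out rate is stated.

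**The concern.** A classical repeated measures ANOVA can use a man only if he has a value at T0, T1 and T2. Missed visits are foreseeable here. Follow-up runs to six months after an eight-week programme, the Background describes the men's rosters as unpredictable, and retention is itself a target of estimation. What happens to a man who attends T0 and T1 but misses T2 therefore decides what the time analysis means.

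The stated rules allow two answers. Under the exclusion rule he leaves the time analysis and his T1 value goes with him. Under the replacement rule he stays, with an invented T2 value that the ANOVA treats as observed. The first can bias the estimated change if the men who return differ from those who do not. The second understates the error variance. The study is meant to inform the design and sample size of a later trial, so a distorted change estimate would carry forward.

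**Working it through.** **Inputs.** From the document: three visits, n = 38 (taken here as the total, because the article does not say whether it is total or per arm), and alpha 0.01. The article gives no missed-visit rate, no within-man correlation and no figure for the time analysis, so there is no plan figure to reproduce. Those quantities are assumed below and shown as ranges.

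**Step 1: what the 10% rule does to a missed visit.** A questionnaire never completed is 100% missing, and 100% exceeds 10%, so literally it is excluded before any replacement. The eating-habits outcome comes from that questionnaire. BMI and waist-to-hip ratio are measured by the researcher, so the rule does not plainly cover them. For those outcomes the ANOVA still needs all three values or a replacement.

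**Step 2: how many men remain as completers.** If each follow-up visit is missed independently with probability m, completers = 38 × (1 − m)². If only T2 is missed, completers = 38 × (1 − m).

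| m | both visits can be missed | only T2 can be missed |
|---|---|---|
| 5% | 34.3 | 36.1 |
| 10% | 30.8 | 34.2 |
| 20% | 24.3 | 30.4 |
| 30% | 18.6 | 26.6 |

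**Step 3: completers under random drop-out.** Take 10% missing at T1 and about 23% at T2. Completers number 38 × 0.9 × 0.77 = 26.3, and men with both T0 and T1 number 38 × 0.9 = 34.2. With unit variance, the SD of the mean T0-T1 change is √(2(1 − ρ)/n):

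- ρ = 0.5: √(1/26.3) = 0.195 for completers, against √(1/34.2) = 0.171 for all T0-T1 pairs.
- ρ = 0.7: √(0.6/26.3) = 0.151, against √(0.6/34.2) = 0.132.

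That is 14% larger from discarded pairs alone (√(34.2/26.3) = 1.14). In simulation, maximum likelihood on all observed visits gave 0.13-0.16 against 0.15-0.19 for completers, roughly 15-20% larger (repeat runs spread from 12% to 24%). The test itself stayed valid: 0.011 at nominal 0.01 in a separate simulation (6000 trials, ρ = 0.6, about 20% missing T2).

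**Step 4: completers under selective drop-out, no true change.** T2 drop-out (26-32%) was made a logistic function of the T0-T1 change, with 10% random missingness at T1.

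- Moderate dependence (slope 1): false T0-T1 shift of 0.14-0.23 SD, with 3-5% rejection at nominal 1%.
- Strong dependence (slope 2): false shift of 0.26-0.40 SD, with 12-19% rejection.
- The 6000-trial simulation, with slope 1.5 and T1 always observed, gave a shift of 0.098 − (−0.097) = 0.195 SD and 5.6% rejection.
- Likelihood estimates on all observed visits showed bias within about 0.03 SD.

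**Step 5: single replacement of T2, no true change.** Rejection at nominal 0.01, from the same 6000 trials (simulation error about √(0.01 × 0.99/6000) = 0.0013):

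| T2 missingness depends on | complete case | mean replacement | regression replacement |
|---|---|---|---|
| nothing (random) | 0.011 | 0.022 | 0.027 |
| T0 | 0.019 | 0.064 | 0.028 |
| T1 | 0.018 | 0.059 | 0.028 |
| T0-T1 change | 0.056 | 0.022 | 0.027 |

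Replacement is too liberal in every row, even under random drop-out, where the complete-case test is sound.

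**The case against.** A reader might infer that the plan keeps only men seen at all three visits. The article does not say so. It commits to intention-to-treat and allows replacement of missing data in general terms, and a replaced visit would keep the man in the ANOVA. This stands, and completer-only analysis is therefore one reading of the rules, not a stated procedure. It does not rescue the analysis, because Step 5 shows that the replacement route is also defective.

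A reader might also infer that one missed visit deletes a man from the trial's results. It does not. The t and chi-square tests do not need all three visits, and the three main research questions concern differences between groups.

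Nor is a false time effect inevitable. It needs selective drop-out, and the 12-19% figure needs the strongest dependence that was assumed. The near-zero likelihood bias follows partly from the set-up, since drop-out was made to depend only on observed T0 and T1 values.

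Finally, detail on missed visits may sit in a full protocol or SAP that is not shown. That is fair as to silence. The point here rests on what is stated: a method that needs every visit, an exclusion threshold that a missed visit exceeds, and single replacement as the alternative.

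**Conclusion.** The point holds for the time analysis only. On one reading of the stated rules the ANOVA rests on completers, in tension with intention-to-treat. On the other it uses single replacement and rejects in about 2-6% of trials at a nominal 1%. For completers, the cost is precision alone under random drop-out, and a false shift of 0.14-0.23 SD with 3-5% rejection under moderate dependence on the T0-T1 change.

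The sizes rest on 38 men, compound symmetry with correlation 0.5-0.7, about 20-30% missing at T2 and no clustering by station. They indicate the scale of the problem and do not predict this trial's drop-out. In an exploratory feasibility study this is worth correcting, but it does not invalidate the between-group comparisons.

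**What to change.** In the Data analysis section:

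1. For continuous outcomes, replace the repeated measures ANOVA with a linear mixed model (SPSS MIXED, REML). Fit visit as a categorical factor, arm, and arm-by-visit, with a within-man covariance. Use every observed visit and do not replace missed visits.
2. State that the 10% rule applies to the questionnaire at that visit and does not remove a man's other visits. Without this, usable visits could still be discarded before the model is fitted.
3. Keep the complete-case ANOVA as a sensitivity analysis.

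The cost is a few sentences and slightly more analysis work, with the same data and software and no extra visits. The model does not cure drop-out that depends on unobserved values, and the report should say so. Because the Trial status section records the study as completed, the change should be dated and marked as made before or after the outcome data were examined.

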## Methods/design

### Study design

A two-armed, pre-post test, clustered randomized control trial (CRCT) design will be used in this study. Figure 1 shows the overall design. The data will be collected at three time points: T_0_, baseline; T_1_, 3 months after the completion of an 8-week intervention; and T_2_, 6 months after the intervention.

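### The sample size is framed with 95% confidence and 80% power, but every comparison is tested at P < 0.01, so the stated power does not apply to the threshold used

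*Protocol article*

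**What the plan says.** The Sample size section of the protocol article states: "The proposed sample size was calculated to be 38". One sentence gives two grounds for that number. The first is precision, namely "estimation of the feasibility proportions of adherence and retention to within at least ±17" per cent. The second is a between-group aim. Both are joined to a single level: "using a 95% confidence interval with a power of 80% to detect an effect size of 0.6". The section names no alpha, no sidedness and no test, and does not say whether 38 is the total or the number per arm.

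The Study design section describes two arms with clusters as the unit of randomisation. Under Data analysis, t tests and chi-square tests are the planned between-group methods ("Differences between the intervention and control groups on outcome indicators will be compared using" these). The same section gives the article's only rule for significance: P "values of less than 0.01 will be considered as statistically significant for all comparisons". It offers no reason for 0.01, such as a multiplicity adjustment, and does not link it to the sample size.

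**The concern.** A power figure has meaning only at a stated test level. The one level printed next to the 80% is 95%, which on the ordinary reading is a two-sided 5% test. The analysis tests at 1%. A reader who takes the sample size statement at face value will believe that the trial has an 80% chance of declaring an effect of 0.6 significant. Under the trial's own rule the chance is much lower.

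This matters because Study aims poses three between-arm questions, on eating habits, BMI and waist-to-hip ratio, and the Discussion says that the findings will be the foundation for a bigger project. If a non-significant result is read against a nominal 80% power, it looks like evidence against the intervention when it is close to uninformative.

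**Working it through.** **Inputs.** From Sample size: 38 participants, 95% interval, 80% power, effect size 0.6, precision ±17%. From Data analysis: t test for continuous outcomes, threshold P < 0.01. From Study design: two arms.

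**Assumptions not in the article.** Equal allocation, the effect size taken as a standardised mean difference, two-sided testing, and no inflation for clustering.

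**1. The article's own figure: precision.** The half-width is z × √(p(1−p)/n). With z = 1.96, p = 0.5 and n = 38, it is 1.96 × √(0.25/38) = 0.159, or ±15.9%. The ±17% target is met. The minimum n is 1.96² × 0.25 / 0.17² = 33.2, so 34. An allowance of 10% for dropout would give 34/0.90 = 37.8, so 38, but no dropout rate is stated. At 99% confidence the half-width with 38 would be ±20.9% and the target would be missed. The 95% therefore fits the precision aim.

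**2. The article's own figure: power at 5%.** The normal approximation is n per arm = 2(z₁₋α/₂ + z₀.₈₀)² / d² = 2(1.960 + 0.842)² / 0.36 = 43.6, so 44. The t-based figure is 45 per arm. The 38 is not reproduced, either as a total or per arm.

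**3. Sample size at the level the trial uses.** At two-sided 1%, n per arm = 2(2.576 + 0.842)² / 0.36 = 64.9, so 65. The t-based figure is 67 per arm.

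**4. Power actually available.** The noncentral t has noncentrality d × √(n/2), with n per arm.

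| Reading of 38 | n per arm | Noncentrality | df | Critical t, 5% / 1% | Power, 5% | Power, 1% |
|---|---|---|---|---|---|---|
| Total | 19 | 0.6 × √9.5 = 1.85 | 36 | 2.03 / 2.72 | 44% | 21% |
| Per arm | 38 | 0.6 × √19 = 2.62 | 74 | 1.99 / 2.64 | 73% | 49% |

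The normal approximation agrees: 45.6% and 23.4% for the total reading, 74.4% and 51.6% for the per-arm reading.

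**5. Does another reading rescue the statement?** Some t-based designs come near 38:
- a one-sided 5% two-sample test needs 36 per arm;
- a one-sided 5% paired test needs 19 in each arm, or 38 in all;
- a two-sided 1% paired test needs 36 in total.

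None of these is stated, and a paired test is not the between-arm comparison that the research questions ask about.

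**The case against.** The strongest reply is that the two sections do different jobs. Sample size is a planning statement, and its 95% is worded as a confidence interval. It follows directly on the feasibility proportions, and step 1 shows that 38 fits that purpose. A stricter test level in the analysis is legitimate and conservative. The study is exploratory, with the stated main purpose of collecting data to design and size the later trial.

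Much of this stands. A reader might infer that the article holds two conflicting decision rules, so that P = 0.03 would be positive under one section and negative under the other, with the choice open once the data are seen. The article does not support that. Sample size sets no rule for calling a result positive, Data analysis sets one rule for all comparisons, and P = 0.03 is simply non-significant. Nor does the article plan 95% intervals for between-arm effects, so a clash between a reported interval and its test is not built into the plan.

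The reply does not remove the mismatch. If the 95% belongs only to the feasibility proportions, the 80% power for 0.6 has no test level at all. If it covers both aims, the level differs from the one used. Either way the power claim does not hold at P < 0.01. This is also not a detail left to a fuller document, because the article prints both levels itself.

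**Conclusion.** The point holds as a mismatch between planning and analysis: the 80% power in Sample size does not apply to the threshold in Data analysis. At an effect size of 0.6, power under the trial's rule is about 21% if 38 is the total and about 49% if it is per arm. The corresponding figures at 5% are 44% and 73%. Since 80% power at 5% would already need about 45 per arm, the 1% level worsens a shortfall and is not its only cause.

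These figures rest on the assumptions listed in the working. Stations are randomised, so any positive within-station correlation would lower the power further under the same comparison. The feasibility precision is not affected by this point. The exploratory purpose limits the harm but does not make the statement correct.

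**What to change.** Keep P < 0.01 as the pre-stated rule in Data analysis and add its sidedness. In Sample size, do one of two things:

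- Restate the power at the 1% level, saying which test it refers to and whether 38 is the total or per arm.
- Say that the 38 and the 95% interval serve only the ±17% precision for adherence and retention (±15.9% at a proportion of 0.5), and that between-arm comparisons are exploratory and not powered.

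The second option suits the stated purpose better. If intervals are reported beside the 1% tests, give 99% intervals or say plainly that the interval and test levels differ.

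Moving the threshold to 5% is not recommended as a silent alignment. Trial status reports completion on 29 February 2020, so such a change would loosen the only pre-stated rule and must be disclosed as made after the plan.

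The cost is a few sentences, with no new data or participants. The downside is a less favourable planning statement, and wider intervals if 99% is used: about 2.576/1.960 = 1.31 times the 95% width on the normal approximation.

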### Development of questionnaire

A questionnaire (Additional file 3) has been developed on the basis of several studies [26, 27, 107–110]. This consists of six study aspects: (1) Personal information; (2) Working characteristics; (3) Eating habits; (4) Health promotion programme for healthy eating; (5) Stage of change; and (6) Decisional balance and self-efficacy.

The questionnaire includes 11 items to assess the Hong Kong firefighters’ eating habits, especially their fruit and vegetable consumption. These questions are based on a series of eating habit studies [26, 27, 107, 108]. The consumption of fruit and vegetables will be measured by asking: (1) “How often did you consume fruits/vegetables in the past week?” (responses ranging from “Not consumed” to “Seven days”); (2) “Where do you usually have fruits/vegetables?” (three choices are “At home”, “During duty” or “No difference, at home and during duty”); and (3) “On a day you consumed the fruits/vegetables, how much did you take on average on that day?” (in bowls or servings). For eating habits, the questions also included “On average, how many days do you have breakfast/lunch/dinner/night snack (take away included) within a week?” (responses ranging from “None” to “More than 5 days”) and “How about the speed of having meals when you are on duty in the fire station when compared to the meals you eat at home?” (responses ranging from “Slower” to “Faster”).

Thirty-five questions were designed to understand decisional balance. Based on Ma et al. (2003) [110], they address the pros, cons and self-efficacy of eating fruit and vegetables. The decisional balance will be evaluated by asking the participants how important each of the pros and cons is in their decisions to consume recommended amounts of fruit or vegetables, using 5-point Likert scales ranging from 0 (Not at all important) to 5 (Very important). Eight pros and nine cons for fruit intake and eight pros and ten cons for vegetable intake will be used to assess the decisional balance.

Twelve questions were designed to assess self-efficacy by rating, on 5-point Likert scales ranging from 0 (Very difficult) to 5 (Very easy), how difficult or easy the participants find it to eat based on the recommendations in six high-risk situations, for each of the two dietary habits [109].

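### The 10% questionnaire-completeness rule contradicts the promised intention-to-treat analysis for the questionnaire-based primary outcome

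*Protocol article*

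**What the plan says.** Three statements in the Data analysis section of the protocol article bear on this point.

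- Analysis principle: "Intention-to-treat analyses will be applied".
- Exclusion: the article first concedes that "there is no clear cut-off for the acceptable proportion of missing data in a dataset for statistical data analysis". It then fixes a cut-off: "Questionnaires with missing rates of more than 10% will be regarded as" disqualified "and excluded from the analysis".
- Replacement: "Various statistical methods will be used to treat missing data, including replacement by means or values from the regression analyses", with the choice "depending on the amount and type of missing data".

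The Study aims section names changed eating habits as the primary outcome and BMI and waist-to-hip ratio as secondary outcomes. Under Development of questionnaire, "The questionnaire includes 11 items to assess" eating habits, alongside much longer blocks on decisional balance and self-efficacy. The Body measurements and Data collection sections place the anthropometric data on a separate form, measured by the researcher.

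**The concern.** Intention-to-treat means comparing randomised participants in the arm to which they were assigned. A rule that drops a form because too little of it was filled in selects participants by what they did, and at the two follow-up visits that happens after randomisation. For an outcome that exists only on that form, the principle and the rule cannot both be followed.

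The rule is also poorly aimed. It looks at the whole questionnaire, most of which does not measure the primary outcome, so complete eating-habit answers can be thrown away because of gaps elsewhere. Losing one visit may cost more than that visit. The effect of time is to be tested by repeated measures ANOVA, which in its standard form uses only people with all visits complete. With 38 participants planned, each loss counts.

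A second, conditional concern is the replacement of missing values. If a mean or a regression prediction is inserted once and then treated as an observation, the standard error is too small or the effect is diluted, depending on which mean is used.

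**Working it through.** **Figures available.** The article gives no expected rate of missing data, so there is no planned figure to reproduce. The only inputs are the 10% threshold, the item counts, the sample size of 38, the effect size of 0.6 and the 0.01 significance level. All missingness rates below are assumptions.

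**Step 1: the two rules side by side.** The principle covers everyone randomised. The exclusion removes forms according to completeness. The primary outcome comes from the form. A disqualified form therefore means no primary outcome for that randomised person at that visit, even where the eating-habit answers are present. No arithmetic is needed for this.

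**Step 2: what the threshold counts.** Items stated under Development of questionnaire:

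- eating habits: 11
- decisional balance: 8 + 9 + 8 + 10 = 35
- self-efficacy: 12
- stage of change: 4
- opinion of health promotion: 3

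The total is 11 + 35 + 12 + 4 + 3 = 65. Decisional balance and self-efficacy together make 35 + 12 = 47, and 47/65 = 72%.

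The personal and working-characteristics sections are extra, and the article does not count their items. Reading the missing rate as the share of unanswered items, the smallest number of gaps that exceeds 10% is:

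| Total items | Gaps that disqualify | Rate |
|---|---|---|
| 65 (stated items only) | 7 | 7/65 = 10.8% |
| 70 (assuming 5 more) | 8 | 7/70 = 10.0% is not above 10%; 8/70 = 11.4% |
| 75 (assuming 10 more) | 8 | 8/75 = 10.7% |

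In every row the gaps can all fall among the 47 attitude items, with all 11 eating-habit items answered. In the other direction, on the 65 stated items, a form with 6 of the 11 eating-habit items blank and nothing else missing has 6/65 = 9.2% missing and is kept. The rule does not track completeness of the primary outcome either way.

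**Step 3: replacing whole outcome values, assumed fraction f.** Assume 19 per arm (38/2), individual-level data without clustering, and values missing completely at random.

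*Arm mean.* With o = n(1 − f) observed out of n per arm, naive SE / true SE = √((o − 1)/(n − 1)) × √(o/n), which is close to 1 − f.

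- f = 10%: o = 17.1; √(16.1/18) × √0.9 = 0.946 × 0.949 = 0.90
- f = 20%: o = 15.2; √(14.2/18) × √0.8 = 0.888 × 0.894 = 0.79

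The approximate type I error at nominal 0.01 is 2Φ(−2.576(1 − f)): 2.0% at f = 10% and 3.9% at f = 20%. A simulation of the t test (40,000 runs each) with 2 or 4 of 19 values per arm filled gave 2.2% and 4.2%.

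*Overall mean of both arms.* The expected difference becomes (1 − f) × 0.6, which is 0.8 × 0.6 = 0.48 at f = 20%. The estimate and its standard error shrink together. The simulated type I error at nominal 0.01 stayed at 0.9% to 1.0%.

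**Step 4: replacing single items in a kept form.** With one of 11 items per person filled by the item mean (simulated, 19 per arm), type I error was 1.2% at nominal 0.01 and about 5.4% at nominal 0.05. This is nearly harmless.

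**The case against.** The strongest reply has four parts.

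- **Forms, not people.** The text excludes questionnaires. A reader might infer that the plan removes randomised participants from the trial analysis altogether. It does not say so. BMI and waist-to-hip ratio are recorded separately and nothing says they are dropped, and a poor form at one of three visits need not remove the person from every comparison. This stands for the secondary outcomes. For the primary outcome the visit is still lost, and possibly the person from the repeated measures ANOVA.
- **The replacement list is open.** A reader might infer that the plan commits itself to filling gaps with means. The wording names means and regression values as examples among various methods, does not say which mean, and does not rule out multiple imputation. An article may also leave the final choice to a fuller document. This stands, so the replacement concern is conditional on how the named methods are used.
- **The numerical harms are easily overstated.** The raised type I error belongs to arm means and the dilution to an overall mean, so they do not occur together. Both concern whole missing outcome values, not the odd blank item in a kept form. Nor is 7 of 65 an exact trigger, because the full item count is not in the article. All of this stands and is reflected in the working.
- **Bias is not shown.** Completeness might differ between arms, since one receives WhatsApp material every 2 weeks and the other only a pamphlet, but the article offers no evidence that it does. This stands: differential loss is plausible and not demonstrated.

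None of the four removes the contradiction, which lies in stated rules and not in omitted detail.

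**Conclusion.** The point holds for the questionnaire-based outcomes, above all eating habits. The plan promises intention-to-treat and also prescribes an exclusion that is incompatible with it. Because the threshold covers the whole form, 7 or 8 blank attitude items (7 on the 65 counted items, 8 if 5 to 10 more are assumed) are enough to discard complete primary data. This conclusion needs no assumption about how much is missing; only the exact trigger depends on the uncounted items and on reading the missing rate as unanswered items.

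The replacement part is secondary and conditional. If means or single regression values fill whole missing outcomes, uncertainty is understated. With arm means and an assumed 10% or 20% missing, the error rate at nominal 0.01 is about 2% or 4%. With an overall mean, the error rate is near nominal but a 0.6 SD effect becomes about 0.48 at 20%. These figures assume 19 per arm, no clustering and values missing completely at random. The documents do not support applying them to a few items filled within a retained questionnaire.

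**What to change.** - Delete the 10% disqualification rule.
- Score each outcome from its own items, and analyse every randomised participant who has that outcome in the assigned arm.
- For missing whole outcomes or visits, use a likelihood-based mixed model on the available data that respects the station clusters. Alternatively, use multiple imputation, kept simple enough for about 38 participants. Either takes the place of mean or single-regression replacement.
- Keep the 10% completeness rule only as a sensitivity analysis.
- If the exclusion is kept in the main analysis, do not call that analysis intention-to-treat.

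The cost is revised analysis wording and slightly more analysis work. No new data are needed, provided that the answers on incomplete forms are entered and not set aside. The likelihood-based model and multiple imputation, in their usual form, still rest on a missing-at-random assumption, which should be stated.
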